### Statistical analysis

#### Effect evaluation

Categorical data were summarised as frequency and percentage, and continuous data as mean (SD) or median (range). We will use fixed effects models to analyse the overall effect of our deimplementation strategy on overtreatment of ASB.^25^ To adjust for clustering and temporal trends, we will include the clusters (hospitals) as a categorical predictor and the time in months as a fixed effect in the model. To correct for the level 2 variance, we will multiply the SE estimates by the square root of the design effect (DEFT). We will evaluate the differences between baseline period and intervention period according an intention to treat principle. To adjust for confounders, we will include the main risk factors for overtreatment of ASB (namely, age, acutely AMS and positive urinalysis)^26^ in the model. We will use the Akaike’s Information Criterion and analysis of variance tables to compare the fitting of the models. We will report the results of the adjusted, unadjusted and intercept models. A two-sided p value of<0.05 was considered significant.

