## Methods and analysis

### Study design and setting

For the development of our study protocol, we used the reporting guidelines for stepped-wedge cluster randomised trials.^17^ We will use a repeated measurement stepped-wedge cluster randomised design. The deimplementation strategy will be introduced in the ED of five hospitals (clusters) in the Netherlands (one university and four general teaching hospitals) in six time periods consisting of 1 or 2 months, depending on how many patients will be included in the first month. Therefore, the total study duration is 6–12 months (figure 1). The order in which the participating hospitals will receive the intervention will be randomly determined by an independent data manager. Every cluster will start in control condition, and by the end of the trial, every cluster will have received the intervention. We planned to start our study on 1 May 2020. However, due to the COVID-19 pandemic, the start of our study will be postponed until 1 October 2020.

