**Figure 3 F3:**
[figure not shown]
(A) Algorithm of indications for urinalysis and cultures in symptomatic patients. (B) Algorithm of indications for urinalysis and cultures in asymptomatic patients. *Fever (>38°C), painful urination, urinary urgency, frequent miction, suprapubic pain, flank pain. SWAB, Stichting Werkgroep Antibiotica Beleid (the Dutch Working Party on antibiotic policy); UTI, urinary tract infection.

For the additional local part of the strategy, a local champion, one of the leading physicians, will be appointed in each participating hospital and will be responsible for the deimplementation strategy. The local champion will start an asymptomatic bacteriuria quality improvement team (ASB team), which will consist of at least an emergency doctor, infectious disease physician, a resident internal medicine and a nurse from the ED. The ASB team will be motivated to assess barriers and facilitators within their hospital and to start additional interventions based on the local setting. For example, by educating and/or reminding healthcare workers about appropriate urine testing and treatment for ASB, and evaluating and/or adjusting local protocols to reduce inappropriate urine testing and antimicrobial use. Further, the ASB team will collaborate with the antibiotic stewardship teams. During the intervention period, the project coordinator will be in contact with the local champion and/or the ASB-team once every 2 weeks to exchange ideas and experiences based on interim results (ordering patterns of urine culture) and assessment of local facilitators and barriers.

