### Sample size

We will use a stepped-wedge hospital-randomised design with six time periods and five steps, in which one hospital will switch from control to treatment at each step. Previous studies have shown reduction of inappropriate treatment for ASB of approximately 50% following deimplementation strategies.^8^ Therefore, we anticipate that the proportion of patients who received inappropriate antimicrobial treatment for ASB will be reduced by 50% from 0.450 to 0.225 after the deimplementation strategy. Assuming an intrahospital correlation coefficient of 0.10, a total of at least 420 patients (=14 patients×six time periods×five hospitals) will achieve 80% power to detect this reduction using the two-sided Wald Z-test with a significance level of 0.05. We used PASS V.15.0.10 to calculate this sample size. During the same time period, we will include additional patients with positive urinalyses.

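### The single baseline-versus-intervention effect puts a net 86% of its weight on each hospital's first intervention period, so it can understate or overstate the average reduction if the effect changes with exposure

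*Protocol article*

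**What the plan says.** Under Effect evaluation, the protocol article fixes a fixed-effects model for the overall effect of the strategy, with hospitals as categories and calendar time in months. The contrast is stated as: "We will evaluate the differences between baseline period and intervention period according an intention to treat principle". It names no term for time since the switch, no lag and no transition period.

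The layout is given under Sample size: "six time periods and five steps, in which one hospital will switch from control to treatment at each step". Study design and setting gives the period length: "in six time periods consisting of 1 or 2 months, depending on how many patients will be included in the first month". The power statement treats the whole drop as present throughout the intervention condition: the proportion "will be reduced by 50% from 0.450 to 0.225 after the deimplementation strategy".

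The Deimplementation strategy section describes two parts:

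- **General part.** Education, the feedback report, posters and pocket cards come at the start of the intervention period.
- **Local part.** A team at each hospital is to assess barriers and "to start additional interventions based on the local setting". The project coordinator is in contact every 2 weeks during the intervention period.

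**The concern.** A single on/off effect estimates the average effect over the intervention condition only if every hospital reaches the full effect in its first period and holds it. A strategy with one part delivered at kick-off and another added and adjusted afterwards gives reason to doubt that. The local part could make the effect grow, and a one-off educational start could make it fade.

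In a stepped wedge this is more than a loss of precision. In the later periods, hospitals that switched early act as comparators for those that have just switched. Their longer exposure then enters with little or negative weight, and the estimate is not the average of the effects that occurred. The article states its aim as a 50% reduction, so the size of the estimate matters as well as the p value.

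**Working it through.** **Inputs.** Five hospitals, six periods, one hospital switching per step (Sample size). 14 patients per hospital-period: "a total of at least 420 patients (=14 patients×six time periods×five hospitals) will achieve 80% power". Proportions 0.450 and 0.225, a difference of 22.5 points. "Assuming an intrahospital correlation coefficient of 0.10". Test: "using the two-sided Wald Z-test with a significance level of 0.05". Hospital and time effects come from Effect evaluation. Equal cells and a linear (risk-difference) fit are assumptions.

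**1. The plan's power figure.** Use the Hussey-Hughes variance with mean proportion 0.3375.

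- Within-hospital variance: 0.3375 × 0.6625 = 0.2236; per cell s² = 0.2236/14 = 0.01597.
- Between-hospital variance: t² = (0.10/0.90) × 0.2236 = 0.02484.
- Design sums: U = 15, W = 55, V = 55, so IU - W = 20 and U² + ITU - TW - IV = 225 + 450 - 330 - 275 = 70.
- Variance = 5 × 0.01597 × (0.01597 + 6 × 0.02484) / (20 × 0.01597 + 70 × 0.02484) = 0.00640; SE = 0.080.
- Power = Φ(0.225/0.080 - 1.96) = 80.3%. The stated 80% is reproduced. It assumes the full effect in every intervention cell.

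With hospitals as fixed effects, as in the planned analysis, the variance is (30/70) × 0.01597 = 0.00684, SE = 0.083 and power about 78%. The power figures below use this SE. They leave out covariate adjustment and the planned design-effect multiplier on the SE. A multiplier above 1 would lower every power figure but would not change the weights.

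**2. Weights by exposure period.** Hospital i (in order of switching) is in exposure period s at study period i + s. Removing hospital and period means from the treatment indicator leaves 0.7 - 0.2s - i/30 in that cell. The sum of squares over all 30 cells is 70/30 = 2.333. Sum over the hospitals that reach exposure s and divide by 2.333:

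| Exposure period | Hospitals | Sum | Net weight |
|---|---|---|---|
| 1 | 5 | 2.000 | 0.857 |
| 2 | 4 | 0.867 | 0.371 |
| 3 | 3 | 0.100 | 0.043 |
| 4 | 2 | -0.300 | -0.129 |
| 5 | 1 | -0.333 | -0.143 |

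The weights sum to 1. They are the same with time as categories or as a linear term. With 2-month periods and monthly effects, the first two months carry 2 × 0.429, again 0.857. A random-effects model at a correlation of 0.10 would give 0.80 for the first period.

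**3. What the weights do under assumed curves.** The expected estimate is the sum of weight × effect. The cell average weights exposure periods 1 to 5 by 5, 4, 3, 2 and 1 out of 15.

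| Assumed curve (share of full effect) | Expected estimate | Cell average | Power |
|---|---|---|---|
| Constant | 100% (22.5 points) | 100% | 78% |
| 0.5, then 1 | 57% (12.9 points) | 83% | 34% |
| 1/3, 2/3, then 1 | 30% (6.9 points) | 69% | 13% |
| 1, 0.8, 0.6, 0.4, 0.2 | 110% (24.8 points) | 73% | 85% |

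For example, row two is 0.5 × 0.857 + 0.371 + 0.043 - 0.129 - 0.143 = 0.571. Its cell average is (2.5 + 4 + 3 + 2 + 1)/15 = 0.833, and its power is Φ(0.571 × 0.225/0.083 - 1.96) = 34%. Logistic fits to similar curves gave similar ratios on the log-odds scale: 0.58 for half then full, 1.00 for constant and 1.07 for waning.

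**4. Alternatives (same inputs, categorical periods).**

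| Estimate | SE | Variance relative to on/off |
|---|---|---|
| On/off effect | 0.083 | 1 |
| One term per exposure period, cell-weighted average | 0.113 | about 1.9 |
| One term per exposure period, equal weights | 0.135 | 2.7 |
| First period separate, later effect | 0.109 | 1.75 |

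The later-period coefficient of the two-term model weights exposure periods 2 to 5 by 0.95, 0.30, -0.075 and -0.175. Under the one-third ramp it gives 0.95 × 2/3 + 0.30 - 0.075 - 0.175 = 0.68, against a true later average of (4 × 2/3 + 3 + 2 + 1)/10 = 0.87. Under waning it gives 0.875 against 0.60. It repairs a lag confined to the first period and nothing more.

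**The case against.** The strongest reply is that nothing in the article says the effect grows with exposure. The general part is delivered at the start to all emergency department staff, with e-mails to those who miss the meeting. The local champion helps lead the kick-off, and Data collection says that baseline data feed the local strategy. A reader might infer that the local strategy is built only after kick-off and that the estimate will therefore be too small. The text does not support either step: preparation begins earlier, and waning reverses the sign. That part of the reply stands.

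A reader might also infer that the trial would declare its target missed. The article contains no such rule. The 50% figure is an aim and a sample-size assumption, and the test is against no effect.

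It is also true that one common effect with hospital and time terms is a recognised stepped-wedge model, that it keeps its validity under no effect, and that sensitivity analyses are often left to an analysis plan that is not shown here. This limits the point to the reported size of the effect and to power. It does not remove it, because the article does fix the contrast, and the weights follow from that contrast and the layout, whatever effect curve is assumed.

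**Conclusion.** The point holds in conditional form. The planned estimate equals the average effect over treated hospital-periods when the effect is immediate and constant. If the effect builds up or wanes, it can miss that average by a wide margin in either direction: 57% against 83% for half then full, and 110% against 73% for the waning curve. Under build-up, power also falls well below the planned 80%. The direction cannot be known from the documents, so a claim that the reduction will be underestimated goes too far.

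The weights rest on equal hospital-period sizes and a linear fit. The sizes rest on effect curves that are assumptions. The test of no effect is not in question.

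**What to change.** Keep the on/off model as the primary test. Before outcome data are analysed, pre-specify beside it a model with hospital and categorical period effects and a separate term for each exposure period, and report the average effect over treated hospital-periods with its interval. Base any statement on the 50% aim on both estimates, and say so where they differ.

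A two-term model (first period, later periods) may be added, with the note that it is unbiased only if the effect is constant after the first period.

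No new data are needed. The cost is precision: for a 22.5-point effect, the cell-weighted average has power of about Φ(0.225/0.113 - 1.96) = 51%, the equally weighted average about 39% and the two-term later effect about 54%. The effect in exposure period 5 rests on one hospital. These are therefore supporting estimates and should not replace the primary test.

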For the general strategy, we will start the intervention period by holding one or more educational meetings about overtreatment of ASB for all healthcare workers in the ED. During these educational meetings, we will inform all healthcare workers about the current ASB guidelines and discuss the local barriers and facilitators to reduce its overtreatment. Next to this, the results of the baseline period will be used as competitive feedback report between the participating hospitals. This competitive feedback report will be used to raise awareness among healthcare workers.^23^ During this meeting, we will distribute posters and pocket cards with an algorithm (figure 3A, B) for appropriate indications for urine cultures and urinalysis, and overtreatment of ASB, based on current guidelines.^5 24^ The kick-off meeting will be led by the project coordinator and the local champion. These tools will be available throughout the intervention period and after the intervention period, if necessary. We will send emails with the anonymous feedback report and the algorithm to healthcare workers who were not able to join the meeting.

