#### Economic evaluation

We will primarily perform a cost-effectiveness analysis, in which we evaluate the cost effectiveness ratio (CER) (CER=cost of deimplementation/healthcare cost reduction). Our goal was to achieve a reduction in urine culture, urinalysis and antimicrobial prescriptions, and thereby a reduction in costs. The costs of our deimplementation strategy will be divided in non-recurrent study-related costs and recurrent de-implementation-related costs. Non-recurrent study-related costs include material costs, developmental costs of the deimplementation strategy and costs of evaluation of the deimplementation. Recurrent costs include the costs to introduce the deimplementation strategy, such as time of the extra meetings of the ASB team and time invested by the local champion. For feasibility reasons, we will use the number of all urine cultures, urinalyses and antimicrobial prescriptions, representing the main cost benefits due to our strategy. The costs for urine cultures, urinalyses and antimicrobials used in the analyses will be based on Dutch guideline on healthcare economic evaluations.^28^ The result of the cost-effectiveness analysis will be used in a budget impact analysis to assess the financial impact on the hospital’s budget to implement and sustain the deimplementation strategy.

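### The adjusted model treats positive urinalysis as a confounder, although the strategy is designed to change urinalysis use, so the adjusted estimate need not be the total effect

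*Protocol article*

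**What the plan says.** The Effect evaluation section of the protocol article fits fixed effects models with hospital and time, and then adds, as confounders, "the main risk factors for overtreatment of ASB (namely, age, acutely AMS and positive urinalysis". It also states: "We will report the results of the adjusted, unadjusted and intercept models". Fit is compared with "Akaike’s Information Criterion and analysis of variance tables to compare the fitting of the models".

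Other sections make urinalysis something the strategy acts on:

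- Deimplementation strategy: staff receive "posters and pocket cards with an algorithm (figure 3A, B) for appropriate indications for urine cultures and urinalysis", and local teams may change local protocols so that fewer inappropriate urine tests are done.
- Primary and secondary endpoints: the number of urinalyses per 1000 patients in the emergency department (ED) is a secondary endpoint.
- Economic evaluation: "Our goal was to achieve a reduction in urine culture, urinalysis and antimicrobial prescriptions".

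Table 1 defines a positive urinalysis by its results, so the variable can be positive only if the test was done. The primary endpoint is the percentage treated among patients with ASB, which Table 1 defines by culture.

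**The concern.** A confounder must not itself be a consequence of the exposure. Positive urinalysis does not meet that condition with any certainty. In intervention periods it is recorded after the hospital has switched, and whether the test is ordered is one of the things the strategy sets out to change. The article also calls it a main risk factor for overtreatment. A variable that the intervention can change and that predicts the outcome is a candidate mediator: fewer urinalyses, fewer positive results that prompt a prescription, less overtreatment.

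The random order of switching protects the comparison of intervention with control periods. It does not protect a comparison made within levels of a variable measured after the switch. At stake is the primary estimate: the Sample size section powers the trial for the total change in overtreatment, from 0.450 to 0.225, while the urinalysis-adjusted model may estimate only the part that does not run through urinalysis.

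**Working it through.** **1. The plan's own figure.** Inputs from the Sample size section: 5 hospitals, 6 periods, one hospital switching per step, 14 patients per hospital-period, proportions 0.450 and 0.225, intrahospital correlation 0.10, two-sided Wald Z-test at 0.05. The Hussey and Hughes variance for a cross-sectional stepped wedge is

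Var = I·s²(s² + T·t²) / [(I·U − W)·s² + (U² + I·T·U − T·W − I·V)·t²]

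- Total variance: 0.45 × 0.55 = 0.2475
- Between hospitals: t² = 0.10 × 0.2475 = 0.02475
- Cell mean: s² = 0.90 × 0.2475 / 14 = 0.01591
- Design sums: U = 15, W = 55, V = 55
- Numerator: 5 × 0.01591 × (0.01591 + 6 × 0.02475) = 0.01308
- Denominator: 20 × 0.01591 + 70 × 0.02475 = 2.0507
- SE = √(0.01308 / 2.0507) = 0.0799
- Power = Φ(0.225 / 0.0799 − 1.96) = 0.804

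With 13 per cell (390 patients) power is 0.777. The stated 420 is therefore reproduced, and it is the total reduction of 0.225 that is powered.

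**2. What adjustment does to that effect.** Let q0 be the share of ASB patients with a positive urinalysis under control, r the relative fall in that share under the intervention, and d the difference in treatment risk between patients with and without a positive urinalysis, taken as equal in both conditions. On the risk-difference scale:

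adjusted reduction = 0.225 − q0 × r × d

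The article gives none of q0, r or d. All three are assumptions, with q0 = 0.70 throughout. Power uses the SE from step 1, and so ignores any small gain in precision from the covariate.

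| r | d | q0 × r × d | Adjusted reduction | Share of 0.225 removed | Power at 420 |
|---|---|---|---|---|---|
| 0 | any | 0 | 0.225 | 0% | 0.80 |
| 10% | 0.20 | 0.014 | 0.211 | 6% | 0.75 |
| 10% | 0.40 | 0.028 | 0.197 | 12% | 0.69 |
| 30% | 0.20 | 0.042 | 0.183 | 19% | 0.63 |
| 30% | 0.30 | 0.063 | 0.162 | 28% | 0.53 |
| 50% | 0.20 | 0.070 | 0.155 | 31% | 0.49 |
| 50% | 0.30 | 0.105 | 0.120 | 47% | 0.32 |
| 50% | 0.40 | 0.140 | 0.085 | 62% | 0.19 |
| −10% (share rises) | 0.20 | −0.014 | 0.239 | −6% (inflated) | 0.85 |

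**3. Check by simulation.** A large-sample fixed-effects model with hospital and period terms, at q0 = 0.70, r = 30% and d = 0.20, gave −0.224 without urinalysis and −0.183 with it. With r = 0 both models gave −0.226. The formula and the simulation agree.

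**The case against.** The strongest objection is that the mediating path is not shown in the patients who are analysed. The primary population is defined by culture. The article supports fewer urinalyses and cultures in the ED as a whole; it does not say that the share of positive urinalyses falls among patients with ASB. Fewer tests may mainly shrink the denominator. This stands, and it makes both the size and the direction of the problem unknown.

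The article also promises the unadjusted model, so an estimate free of urinalysis will appear next to the adjusted one. That stands too and limits the harm. It does not remove it, because the text presents the urinalysis-adjusted model as the one corrected for confounding, and that is the one readers will tend to trust.

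Four stronger readings are tempting, and the document does not support them:

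- A reader might infer that adjustment will usually pull the effect towards zero. If culturing becomes concentrated in patients with a positive urinalysis, the share rises and the effect is inflated. The link function is not stated either; in a logistic model, adjusting for a strong predictor tends by itself to move the odds ratio away from the null.
- A reader might infer that the best-fitting model becomes the main result. The article uses the fit criteria only to compare models. Naming one primary model may be left to an analysis plan that is not shown.
- A reader might infer that patients cultured without a urinalysis will be dropped or recoded. The article says nothing on this, and it too may be left to the analysis plan.
- A reader might picture the whole effect running through urinalysis, so that adjustment leaves nothing. The education and feedback also address treatment directly, so that is an extreme case.

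Finally, the unadjusted estimate is not a perfect benchmark. If fewer patients are cultured, the mix of patients who enter the ASB denominator may change, and urinalysis status may partly reflect that change.

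**Conclusion.** The concern holds in a conditional form. Positive urinalysis is labelled a confounder, yet it is observed after the switch and depends on a test that the strategy targets, counts as an endpoint and aims to reduce. The adjusted estimate therefore cannot be relied on as the total effect that the sample size is built on. It is that effect only if the share of ASB patients with a positive urinalysis does not change between conditions.

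The size rests entirely on assumed values: from no loss if the share is unchanged, through 6% to 62% of the planned reduction over the range of falls examined, to a modest overstatement (0.239 against 0.225) if the share rises by 10%. The stated sample size is not in question. The point deserves correction before analysis because it concerns the primary endpoint and is cheap to put right, but it does not invalidate the trial.

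**What to change.** Take positive urinalysis out of the main adjusted model. Adjust for hospital, time and characteristics that the intervention cannot plausibly change. Age qualifies. Acutely altered mental status should stay only if its documentation is judged unaffected by the intervention, since it too is taken from records made after the switch. Report the urinalysis-adjusted model as secondary or exploratory, and say that it does not estimate the total effect. It would help to tabulate, by condition, the share of ASB patients with a positive urinalysis, so that readers can see whether r differs from zero.

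The cost is a change of wording and a little lost precision from giving up a predictive covariate; data collection and sample size are unchanged. The change does not cure any shift in who is cultured and so enters the ASB denominator.

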## Introduction

There is a growing urgency to improve healthcare quality and save costs by implementing practices to reduce unnecessary diagnostics, diagnostic error and related overtreatment, so-called low-value care practices. This is exemplified by international campaigns, such as Choosing Wisely and Do not Do prompts, which were launched to reduce unnecessary care in several medical services, resulting in less risks for the patients, saving costs and increasing value for care.^1 2^ A parallel campaign initiative titled ‘To Do or Not to Do?’ was introduced to deimplement unnecessary care in the Netherlands.^3^

Antimicrobial resistance, as a result of antibiotic overconsumption, is a global threat to public health, and there is global consensus about reducing the use of antibiotics.^4^ Urinary tract infections (UTIs) are one of the most common categories of infections for which antimicrobials are prescribed.^5^ However, not all antimicrobial prescriptions are necessary. This is especially true for asymptomatic bacteriuria (ASB), which is the presence of bacteria in the urine of a patient who does not have symptoms of a UTI. ASB is a common finding, especially among women, elderly and patients with urinary catheters. The prevalence of ASB in adults over 65 years is high since the prevalence of ASB increases with age.^6^ Guidelines strongly recommend not to screen for or treat ASB with antimicrobials, except for specific patients at risk of developing a complicated UTI.^5^ This is also outlined in the American Choosing Wisely campaign, which judges treatment of ASB as one of five low-value care services that should be avoided.^7^ In 2015, this resulted in the recommendation ‘Do not use antimicrobials to treat bacteriuria in older adults unless specific urinary tract symptoms are present’.^7^

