†A urinary catheter in situ could cause patient complaints of frequency, urgency or dysuria. Therefore, these symptoms cannot be used in patients with catheters.

ASB, asymptomatic bacteriuria; CFU, colony-forming unit; UTI, urinary tract infection.

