### Data collection

The study will collate a list of all urine cultures and urinalyses performed in the ED, including corresponding microbiology laboratory and clinical chemistry data. All relevant patient information, including the presence of other possible infections, of those with positive cultures will be reviewed from medical and nursing records by a research physician to determine if patients have ASB. For patients with ASB, we will collect data on antimicrobial treatment, including antimicrobial prescription and duration of antimicrobial therapy, and the specified bacterial count and pathogen according to the standard operating procedure of the microbiology laboratory. For feasibility reasons, a random sample of a total number of 220 negative urine cultures will be screened by medical record review to evaluate the indication for testing during the baseline period. We will use these data in the further development of an additional local deimplementation strategy based on the assessment of determinants of current practice. Furthermore, we will collect the patient-level variables, including patient characteristics (age, gender and residency in nursing home), Charlson Comorbidity Index,^19^ Modified Early Warning Score,^20^ chronic urinary catheter use, reason for presentation at the ED and use of antimicrobials for uropathogens in the last 7 days before presentation at the ED. We will also collect the reasons for urine testing documented in the medical record. Data from medical records will be collected in an electronic GCP-compliant database, and we will audit a random sample of 10% to assure the validity of data collection.

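### The adjusted primary model omits catheter use, nursing-home residence and sex, all already collected, so a case-mix change at the switch could bias the effect

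*Protocol article*

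**What the plan says.** **Model.** Under Effect evaluation, the Protocol article states: "we will include the clusters (hospitals) as a categorical predictor and the time in months as a fixed effect in the model". For confounding it adds "the main risk factors for overtreatment of ASB (namely, age, acutely AMS and positive urinalysis" and cites a source for that list. The wording makes the list a closed one. It also states: "We will report the results of the adjusted, unadjusted and intercept models". Models are to be compared by Akaike's criterion and analysis of variance tables.

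**Data.** Under Data collection, the patient-level variables include "patient characteristics (age, gender and residency in nursing home" and "chronic urinary catheter use". Of these, only age is in the model.

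**Who is analysed.** Under Patient selection, patients are found through a urine test done in the emergency department. Under Deimplementation strategy, posters and pocket cards cover when to test, and local teams may change protocols to reduce inappropriate testing. The number of tests is a secondary endpoint, and fewer tests is a stated aim of the economic evaluation.

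**Catheters.** The footnote to Table 1 says of urgency, frequency and dysuria: "these symptoms cannot be used in patients with catheters". The legend of Figure 3, the algorithm handed out at the switch, lists painful urination, urgency and frequent miction among the symptoms. The text shown gives no exception for catheters there; the figure itself is not available.

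**The concern.** In most cluster trials a short covariate list is a matter of taste. Here the analysed group is formed after the switch, by a testing decision that the intervention is meant to alter. If testing falls more in some kinds of patient than in others, the ASB patients detected after the switch differ from those detected before. If those kinds of patient also differ in their chance of being treated, part of the before-after difference reflects case mix and not prescribing.

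Catheter use is the clearest candidate. A catheterised patient with urgency, frequency or dysuria and no other qualifying sign is classed as ASB by the trial, while the listed symptoms of the algorithm may lead the clinician to see a symptomatic patient. Such patients may be treated more often than other ASB patients. If their share changes at the switch, the primary estimate moves with it. At stake is an effect planned with 80% power and little reserve.

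**Working it through.** **1. What hospital and time terms remove.** Write the treatment risk as hospital effect + period effect + θ × intervention + γ × C, where C is an omitted patient marker. Let the prevalence of C be a hospital part + a period part + δ × intervention. Without C in the model, the intervention coefficient estimates θ + γδ. The hospital and period parts are absorbed; the term γδ is not. All other terms held, the bias is the prevalence shift at the switch (δ) times the risk difference for the marker (γ). It is zero if either is zero.

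**2. The plan's own figure.** Inputs from Sample size: 0.450 to 0.225, intrahospital correlation 0.10, 5 hospitals, 6 periods, 14 patients per cell, two-sided 0.05. I used the Hussey-Hughes variance.
- Total variance 0.45 × 0.55 = 0.2475. Between hospitals τ² = 0.02475; cell-mean variance s² = 0.22275/14 = 0.01591.
- Design sums: U = 15, W = 55, V = 55.
- Variance = 5 × 0.01591 × (0.01591 + 6 × 0.02475) / (20 × 0.01591 + 70 × 0.02475) = 0.00638, so SE = 0.0799.
- Power = Φ(0.225/0.0799 − 1.96) = 80.4%.

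The stated 420 is reproduced and does not depend on the covariate list.

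**3. Size of a possible bias.** The documents give neither δ nor γ, so all values are assumed. The marker starts at 20% of control ASB patients, with a higher treatment risk.

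| Share after switch | Risk difference | Bias δγ | Share of 0.225 | Expected estimate | Power at SE 0.0799 |
|---|---|---|---|---|---|
| 20% (no shift) | any | 0 | 0% | −0.225 | 80% |
| 30% | 0.20 | 0.10 × 0.20 = 0.020 | 9% | −0.205 | 73% |
| 30% | 0.30 | 0.10 × 0.30 = 0.030 | 13% | −0.195 | 68% |
| 35% | 0.30 | 0.15 × 0.30 = 0.045 | 20% | −0.180 | 62% |

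A simulation of the three shifted cases (4000 runs each, linear model with hospital and period effects) gave −0.205, −0.196 and −0.178 without the marker, and −0.225, −0.226 and −0.223 with it. With smaller inputs, a shift of 0.05 and a risk difference of 0.05, the bias is 0.0025, or 1%. A shift in the other direction would overstate the reduction by the same amount.

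**4. All three variables together.** In a second simulation (600 runs per setting; assumed prevalences 0.65, 0.25 and 0.20, each rising by 10 points at the switch), the linear estimate was −0.197 without and −0.222 with the covariates when each had an odds ratio of 1.5. The gap of 0.025 is 11% of 0.225. With an odds ratio of 2 it was −0.172 against −0.218, a gap of 0.046 or 20%.

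**5. Precision, with no shift.** The linear SE was 0.080 without and 0.080 with the covariates at odds ratio 1.5, and 0.081 and 0.078 at odds ratio 2. The logistic SE rose, from 0.390 to 0.398 and from 0.389 to 0.406, with power nearly unchanged.

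**6. Events.** The wedge has 15 control and 15 intervention cells, 210 patients each: 210 × 0.45 + 210 × 0.225 = 142 expected treated patients.

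**The case against.** The case against is substantial.

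- **The list is prespecified and sourced.** Nothing in the article shows that it is wrong, and the omission contradicts nothing. This stands: the point concerns a choice that can be improved, not an error.
- **No stated link to treatment.** The Introduction says "ASB is a common finding, especially among women, elderly and patients with urinary catheters". A reader might infer that sex and catheter use therefore confound the effect. That sentence concerns who has ASB. Everyone in the primary analysis has it, so confounding needs a link to treatment given ASB. For sex and nursing-home residence the article states none. For catheter use, the Table 1 footnote read beside the algorithm's symptom list gives a reason to expect one, but that is inference and not data.
- **The same classification rule applies in both periods.** True, so the rule alone causes no bias. A shift in the share of catheterised patients is still needed.
- **Why these three?** The comorbidity index, early warning score, reason for presentation and recent antimicrobial use are also collected. The choice rests on catheter use having a reason in the document, and on all three being fixed before the visit. The case for sex and nursing-home residence is weaker.
- **The simulations leave out age, altered mental status and urinalysis.** Nursing-home residence plausibly overlaps with the first two, so the figures may overstate what the planned model would leave.
- **Imbalance is acknowledged.** The Discussion concedes that few clusters cannot ensure balance. But randomised start times cannot balance a change in testing that the intervention itself causes.

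A reader might also infer that leaving the variables out loses precision. The calculations do not support this: the linear gain is nil to small, and the logistic SE rises.

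**Conclusion.** The point holds in conditional form. The stated model omits three pre-visit variables that the trial collects, in a design where the intervention can change who enters the analysis, and its hospital and time terms do not remove a mix change tied to the switch. It would go too far to read this as showing that the primary effect is biased: the documents support only the possibility of a shift, and give no figure for its size or for the link to treatment. Under the assumed values the bias runs from zero to about one fifth of the planned 0.225 reduction, and its direction is unknown. At the upper end, toward no effect, power would fall from about 80% to about 62%. The stated sample size is unaffected.

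**What to change.** In Effect evaluation, keep hospital, time, age, acutely altered mental status and positive urinalysis, and prespecify chronic urinary catheter use, nursing-home residence and sex as added covariates of the adjusted model. Report it beside the unadjusted model that is already planned, and tabulate the three characteristics by control and intervention period, so that any change in mix can be seen. The additions should be fixed before results are known, because the plan also compares models by fit.

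The cost is about one sentence and one table, with no new data. The downside is three more parameters on about 142 expected events. Adjustment also removes only the measured part of selection through testing; unrecorded reasons for testing or not testing a patient would remain, and the report should say so.
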